## Abstract

**Background:**

Behavioral and psychological symptoms of dementia commonly drive psychotropic prescribing in residential care. Doll therapy is a person-centered, attachment-informed intervention that may reduce distress and support engagement, but evidence from Chinese nursing homes remains limited. This protocol describes an exploratory pilot and feasibility mixed-methods cluster randomized controlled trial of a staff-mediated doll-therapy care package plus routine nursing care versus routine nursing care alone.

**Methods and analysis:**

Phase I is a pragmatic, parallel-group, 1:1 cluster randomized pilot trial in six nursing homes in Zhengzhou, China, targeting 142 residents with dementia. Intervention homes will receive a structured doll-therapy introduction of eight planned sessions over approximately 15 days, continued access to a personal doll during routine care, staff training, structured interaction, relational engagement, and routine-care implementation; control homes will provide routine nursing care alone. Assessments occur at baseline, 6 weeks, and 12 weeks. The registered primary outcome is class-specific mean daily medication dose over 12 weeks for antipsychotics, anxiolytics, and antidepressants, interpreted as an indirect medication-stewardship signal. The main proximal clinical outcome is total Neuropsychiatric Inventory-12 score. Secondary and contextual outcomes include Barthel Index, cognitive enhancer use, traditional Chinese medicine use, and structured engagement with the doll. Phase II uses semi-structured interviews with staff and family caregivers from intervention homes to examine acceptability, implementation, training needs, cultural fit, and ethical considerations. Quantitative analyses will emphasize effect estimates, confidence intervals, cluster-level summaries, and randomization/permutation-based robustness checks; qualitative data will be analyzed thematically.

**Discussion:**

The study will provide feasibility, acceptability, fidelity, safety, preliminary clinical-signal, and implementation evidence to inform a future adequately powered cluster trial in Chinese residential dementia care.

**Trial registration:**

https://clinicaltrials.gov/study/NCT06506487, ClinicalTrials.gov, NCT06506487. Registered July 16, 2024.

## Introduction

Dementia is a major public health challenge associated with population ageing. It is characterized by progressive decline in cognitive function and loss of independence in everyday life, and it is commonly accompanied by behavioral and psychological symptoms such as agitation, anxiety, apathy, depression, wandering, and psychotic phenomena (1, 2). In residential care settings, these symptoms often drive caregiver distress, increase supervision needs, and lead to pharmacological escalation (3, 4). China carries a particularly large dementia burden because of rapid demographic ageing, increasing need for long-term care, and uneven access to diagnostic and care resources across regions (5).

Managing behavioral and psychological symptoms of dementia in nursing homes remains difficult. Antipsychotics, anxiolytics, and antidepressants are frequently used when residents show agitation, aggression, anxiety, or mood disturbance, yet these medications may increase sedation, falls, extrapyramidal symptoms, cerebrovascular events, pneumonia, or mortality risk in frail older adults (4, 6, 7). Non-pharmacological and person-centered interventions are therefore increasingly recommended as a core component of dementia care rather than as an optional add-on (8, 9). However, reductions in psychotropic medication use are not determined by behavioral improvement alone. Prescribing decisions in nursing homes may also be shaped by physician practice, medication-review routines, family preferences, staffing capacity, acute illness, and institutional policies. For this reason, medication-related outcomes in pragmatic psychosocial trials should be interpreted as indirect clinical and service-delivery indicators rather than as simple biological markers of intervention-specific effect.

Doll therapy is one such intervention. In doll therapy, a person living with dementia is offered a lifelike doll and may interact with it by holding, comforting, grooming, or talking to it. Existing reviews and small controlled studies suggest that doll therapy may reduce agitation and support emotional regulation, social interaction, and purposeful activity, but the evidence base remains limited by small samples, variable intervention protocols, inconsistent outcome selection, and incomplete reporting of implementation fidelity and ethical safeguards (10–12). Reported effects appear most consistent for agitation and observable mood-related domains, less consistent for daily functioning, and largely absent for medication-related outcomes such as psychotropic prescribing. Evidence from Chinese nursing homes remains especially limited, with few studies reporting standardized intervention protocols, fidelity monitoring, or medication-stewardship outcomes.

The conceptual rationale for the intervention is informed primarily by attachment theory. Dementia-related losses in memory, orientation, and social familiarity may intensify needs for security, soothing, and emotional regulation. Within this framework, a doll may function as a symbolic attachment object and support caregiving identity, comfort, and meaningful engagement for some residents (13, 14). The hypothesized causal chain from doll therapy to medication-related outcomes therefore involves two distinct steps: (i) a behavioral step in which attachment-informed engagement reduces dementia-related distress behaviors as captured by validated instruments such as the Neuropsychiatric Inventory-12 (NPI-12), and (ii) a prescriber response step in which clinicians and medication-review processes translate behavioral stabilization into reduced or stable psychotropic prescribing. The current pilot protocol does not directly measure attachment processes or formally test mediation; attachment-related mechanisms are inferred theoretically, while engagement records and qualitative interviews provide only indirect contextual evidence. Because the second step depends on prescriber behavior and institutional policy rather than on the intervention itself, any medication-related change observed in this trial will be interpreted alongside more proximal outcomes, particularly NPI-12, Barthel Index, and structured engagement records. In the Chinese care context, this rationale also needs to be considered alongside local cultural understandings of ageing, family caregiving, dignity, institutional care, and the coexistence of biomedical treatment and traditional Chinese medicine in routine dementia care (5, 15).

Doll therapy also remains ethically and culturally sensitive. Concerns have been raised about infantilization, deception, over-attachment, and respect for autonomy and dignity, especially if the intervention is imposed, poorly explained, or treated as a substitute for relational care (16, 17). Acceptability may vary according to residents’ prior life experiences, family expectations, staff attitudes, gendered caregiving histories, cultural beliefs about dolls and old age, and degree of cognitive impairment. These issues are central to the present protocol rather than peripheral implementation details.

Accordingly, the present study uses an exploratory pilot and feasibility mixed-methods design to assess the staff-mediated doll-therapy care package in Chinese residential dementia care. The quantitative phase compares the staff-mediated doll-therapy care package plus routine nursing care with routine nursing care alone on registered medication-related outcomes, NPI-12, Barthel Index, cognitive enhancer use, traditional Chinese medicine use, and participant engagement with the doll over 12 weeks. Because the number of randomized clusters is small, the trial is intended to generate feasibility information, preliminary effect estimates, and implementation signals rather than definitive evidence of clinical effects. The qualitative phase will explore how staff and family caregivers from intervention homes understand, implement, and appraise doll therapy in practice, including ethical concerns and cultural acceptability. Together, these components are intended to inform future larger-scale trials, non-pharmacological dementia care, medication stewardship, and implementation planning in long-term care.

### Aims and exploratory expectations

To avoid overstatement given the limited number of clusters, the study is framed as an exploratory pilot and feasibility trial. Its aims focus on feasibility, preliminary clinical and medication-stewardship signals, and implementation interpretation rather than confirmatory hypotheses about clinical effects.

*Primary registered outcome aim*. To compare class-specific mean daily medication dose for antipsychotics, anxiolytics, and antidepressants over 12 weeks between residents in nursing homes randomized to the staff-mediated doll-therapy care package plus routine nursing care and residents in homes randomized to routine nursing care alone. This aim preserves the registered primary outcome but will be interpreted as an indirect medication-stewardship signal rather than as the dominant endpoint for clinical effects.

*Main proximal clinical outcome aim*. To compare the trajectory of total NPI-12 scores at 6 and 12 weeks between the two arms (main proximal clinical outcome for interpretation).

*Secondary aims*. To compare (i) Barthel Index scores, (ii) cognitive enhancer use, and (iii) traditional Chinese medicine use over 12 weeks between the two arms, and (iv) to describe structured engagement with the doll within the intervention arm.

*Qualitative aim*. To explore how staff and family caregivers in Chinese residential dementia care understand, implement, and appraise doll therapy, including its acceptability, training needs, cultural fit, and ethical implications.

*Exploratory expectations*. Relative to routine nursing care alone, residents exposed to the doll-therapy care package may show (a) lower or stable total NPI-12 scores at 6 and 12 weeks; (b) preserved or improved Barthel Index scores; and (c) no increase in, and possibly a reduction of, class-specific daily psychotropic dose. These directional expectations are hypothesis-generating because the small number of clusters, absence of an active attention-control condition, and indirect nature of medication-related outcomes preclude confirmatory inference.

## Methods and analysis

### Study design

This study uses an explanatory sequential mixed-methods design comprising a quantitative exploratory pilot and feasibility cluster randomized controlled trial (Phase I) followed by a qualitative descriptive study (Phase II) in intervention homes. The sequential structure allows Phase II to interpret and contextualize Phase I findings, particularly with respect to implementation fidelity, acceptability, perceived benefits and harms, and ethical concerns that are difficult to capture quantitatively. Phase I is a pragmatic, parallel-group, 1:1 cluster randomized pilot trial conducted in nursing homes. Phase II is a qualitative descriptive study using semi-structured interviews with staff members and family caregivers from intervention homes. The nursing home is the unit of randomization in order to reduce contamination arising from shared staff routines, activity spaces, care culture, medication-review practices, and everyday communication among residents and staff.

The study will be conducted in six nursing homes in Zhengzhou, Henan, China. Three nursing homes will be allocated to the staff-mediated doll-therapy care package plus routine nursing care and three to routine nursing care alone. Quantitative assessments will be performed at baseline, 6 weeks, and 12 weeks. The protocol is reported in line with SPIRIT 2025 guidance for randomized trial protocols (18, 19); the structured doll-therapy care package is described in line with the Template for Intervention Description and Replication (TIDieR) checklist (20). Because only six clusters are randomized, the study should be read as an exploratory pilot and feasibility cluster trial designed to estimate recruitment, retention, fidelity, safety, acceptability, preliminary effect sizes, and parameters for a future trial. It cannot support robust clinical-effect inference or stable site-adjusted treatment-effect estimation.

Recruitment will commence after all site and ethics approvals are in place and continue until the target sample size is reached. Each enrolled participant will be followed for 12 weeks, and the overall data-collection period is anticipated to span approximately 12 to 15 months.

Patients and members of the public were not involved in the design of the protocol or the preparation of this manuscript, primarily because the research was developed within an existing residential-care service-delivery framework and timeline. Family caregiver and staff perspectives will be captured in the qualitative component, and patient and public involvement will be planned formally for a subsequent definitive trial (Figure 1).

**Figure 1 fig1:**
[figure not shown]
Study flow and assessment schedule for the exploratory pilot and feasibility cluster randomized trial of the staff-mediated doll-therapy care package in residential dementia care.

### Setting, participants, and recruitment

Participating sites are registered nursing homes in Zhengzhou that provide dementia care and agree to comply with the study procedures. After facility-level agreement is obtained, each home will appoint a site coordinator to liaise with the research team, facilitate scheduling, support staff training, and provide access to source documents, medication records, and routine activity records.

Eligible participants must be aged 65 years or older, reside in the participating nursing home, have adequate visual capacity to recognize a doll, and have sufficient upper-limb function to hold or caress a doll safely. Adequate visual capacity is operationally defined as the ability to visually recognize a doll-sized object presented at approximately 30 cm by the screening nurse, regardless of corrected acuity; severe visual impairment documented as functional blindness in the medical record is exclusionary. Sufficient upper-limb function is operationally defined as the ability to hold an object of approximately 1.5 kg with one or both upper limbs for at least one minute in a seated position, without assistance and without pain. Both criteria will be confirmed by a trained nurse during the screening visit and documented on the screening log.

Dementia eligibility requires a documented clinical diagnosis recorded in the resident’s medical or nursing-home record by a qualified physician using DSM-5, ICD-10, ICD-11, or the most recent edition of the Chinese clinical guidelines for the diagnosis and treatment of dementia and cognitive impairment in current use at the participating sites. Where a documented dementia diagnosis exists but the underlying diagnostic criteria are not specified, the site clinician will re-confirm the diagnosis against DSM-5 criteria before enrolment. Mini-Mental State Examination, Montreal Cognitive Assessment, or equivalent baseline cognitive scores will be recorded where available (21). Dementia severity will be classified using the Clinical Dementia Rating scale, the Global Deterioration Scale, or the Functional Assessment Staging Tool where any of these is recorded in the facility’s source documentation. If no validated severity grade is available, the site clinician will assign a categorical severity (mild, moderate, or severe) based on baseline Barthel Index, NPI-12, MMSE (where available), and clinical observation, and the basis for this classification will be documented in the case report form. A legally authorized representative must be available to provide written informed consent, and resident assent will be sought whenever appropriate.

Residents will be excluded if they have acute medical instability; severe sensory or physical limitations preventing safe participation; severe communication impairment that precludes meaningful engagement or assessment of assent/dissent; urgent need for pharmacological or physical restraint; or a major psychiatric disorder unrelated to dementia that would make participation inappropriate. For the purpose of this protocol, major psychiatric disorders unrelated to dementia include documented schizophrenia spectrum disorders, bipolar disorder, current severe major depressive episode with psychotic features or high suicide risk, substance-induced psychosis, or another active psychiatric condition judged by the site clinician to require specialist treatment and to be the primary driver of behavioral symptoms. Residents with depression, anxiety, sleep disturbance, or psychotic symptoms judged to be part of dementia-related neuropsychiatric symptoms will not be excluded on this basis alone.

Potentially eligible residents will be screened from routine clinical records by trained nursing-home staff with oversight from the research team. Written informed consent will be obtained from legal guardians or authorized representatives before baseline assessment. To reduce recruitment bias, resident screening, consent, and baseline data collection will be completed before disclosure of cluster allocation whenever operationally feasible. Screening logs will document the number of residents assessed for eligibility, excluded, consented, and enrolled at each site.

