### Randomization, allocation concealment, and blinding

An independent researcher who is not involved in recruitment, intervention delivery, outcome assessment, data management, or analysis will generate the 1:1 cluster allocation sequence after baseline data collection has been completed for all six participating homes. Because of the small number of clusters, covariate-constrained randomization will be used to reduce the risk of baseline imbalance on prespecified cluster-level characteristics: facility size (number of beds), dementia-care intensity (proportion of residents with dementia), staff-to-resident ratio, and aggregated baseline NPI-12 mean. The allocation algorithm will enumerate all possible 3-versus-3 cluster allocations, retain only those satisfying a predefined balance criterion on these characteristics, and draw one sequence at random from the retained set using R version 4.3 or later. The list of acceptable allocations and the chosen sequence will be archived and reported in the final trial publication. The allocation list will be held separately from site teams and released only to site coordinators after completion of baseline assessment. Baseline cluster descriptors will also be summarized before analysis to confirm balance and to document any residual imbalance for sensitivity analyses.

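### The protocol requires baseline to be complete in all six homes before allocation, but its recruitment section lets screening, consent and baseline follow disclosure when that order is not feasible

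*Protocol article*

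**What the plan says.** Three sections of the protocol article bear on the order of events.

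- **Setting, participants, and recruitment.** To limit recruitment bias, "resident screening, consent, and baseline data collection will be completed before disclosure of cluster allocation whenever operationally feasible". On who screens: "Potentially eligible residents will be screened from routine clinical records by trained nursing-home staff with oversight from the research team".
- **Randomization, allocation concealment, and blinding.** The independent researcher "will generate the 1:1 cluster allocation sequence after baseline data collection has been completed for all six participating homes". The covariate constraint uses facility size, dementia-care intensity, "staff-to-resident ratio, and aggregated baseline NPI-12 mean". The list is "released only to site coordinators after completion of baseline assessment". No exception is given.
- **Study design.** Recruitment is to "continue until the target sample size is reached". On follow-up and total duration, the same section adds: "Each enrolled participant will be followed for 12 weeks, and the overall data-collection period is anticipated to span approximately 12 to 15 months". The text does not say that recruitment closes when the homes are randomized.

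**The concern.** One section makes completed baseline in every home a precondition for an allocation to exist. The other treats baseline before disclosure as the preferred order, to be kept when circumstances allow. A site team reading the second could enrol after disclosure and believe that it was following the protocol.

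That matters in a cluster trial because one disclosure reveals the arm of every later resident in the home. Screening is done by home staff, and the blinding paragraph accepts that direct caregivers and delivering staff cannot be blinded. The site coordinator who receives the allocation is appointed by the home. Several eligibility criteria call for judgement, such as acute medical instability, the capacity for meaningful engagement, and whether a psychiatric condition is the main driver of behaviour. Families' willingness to consent may also differ once they know whether a doll is on offer. The arms could then differ in who was enrolled, in addition to what they received.

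**Working it through.** **1. The plan's own figures.** 128 / (1 − 0.10) = 142.2, which matches the recruitment target of 142, and 142 / 6 = 23.7 residents per home, as stated. Nothing in this point changes these figures.

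**2. The two rules side by side.** Under the randomization section the order is:

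- baseline is complete in six homes;
- the home-level NPI-12 means are computed;
- the 3-versus-3 allocations are enumerated (6 choose 3 = 20) and filtered for balance;
- one allocation is drawn and then released.

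On that order no sequence exists before the last baseline, so nothing can be disclosed early and the exception has nothing to act on. The exception can operate only if the order is broken in one of two ways:

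- (a) the sequence is generated while some baselines are outstanding; or
- (b) baseline is declared complete for those enrolled so far, the homes are randomized, and recruitment then continues towards 142.

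The study design section does not rule out (b).

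**3. Consequence for balance.** Suppose a home has n0 residents with mean NPI-12 m0 at allocation and n1 later enrolees with mean m1. The analysed baseline mean differs from the one used in the constraint by n1 / (n0 + n1) × (m1 − m0). The document gives neither the late share nor the difference, so no figure can be attached.

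**4. Why the planned analysis does not repair it.** The Mancl–DeRouen and Fay–Graubard corrections adjust standard errors and leave the point estimate alone. The permutation check over the retained allocations assumes that, with no treatment effect, each home's data would be the same under any allocation. If enrolment responds to a known arm, that assumption fails even under the null.

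**5. The lag if the strict order is kept.** Baselines then precede a single randomization, so early enrolees wait. The inputs are 12 weeks of follow-up (84 / 30.4375 = 2.76 months) and 12 to 15 months of data collection. The document does not say whether that period includes the Phase II interviews, so the time used only for Phase II is an assumption. The enrolment window is total − 2.76 − Phase II time. With even enrolment, the mean wait is half the window.

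| Assumed time for Phase II alone | Enrolment window | Mean wait |
|---|---|---|
| 0 months | 9.2 to 12.2 months | 20 to 27 weeks |
| 3 months | 6.2 to 9.2 months | 14 to 20 weeks |
| 6 months | 3.2 to 6.2 months | 7 to 14 weeks |
| 9 months | 0.2 to 3.2 months | 0.5 to 7 weeks |

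The window therefore runs from near nil to at most about 9 to 12 months, and the document does not settle where it lies.

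**The case against.** The strongest reply is that the randomization section is the specific, unconditional procedure and is sound. If it is followed, the exception is dead wording and no bias arises. Screening also has research-team oversight, the text does not say who obtains consent, and the trial disclaims confirmatory inference. This stands in part: the bias is conditional on departing from the strict order, and it should not be said that home staff who know the arm will obtain consent. But the recruitment section expressly permits the departure, and recruitment bias would also distort the preliminary estimates that the pilot is meant to supply.

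A reader might infer more than the document supports.

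- **That all three sections are incompatible.** They are not. Recruiting to 142, finishing baselines, randomizing once and then following each resident for 12 weeks satisfies both the study design and the randomization sections.
- **That recruitment rolls for 9 to 12 months.** No duration is stated. That figure is an upper bound which gives Phase II no time of its own.
- **That the trial must have either stale baselines or open-label recruitment.** A short enrolment block before one randomization avoids both. With about 24 existing residents per home, screened from routine records, such a block is plausible.
- **That an old baseline biases the 12-week effect.** Under the strict order, drift before allocation is unrelated to arm and cancels in expectation in the group-by-time contrast. The cost is mainly precision and attrition before the start.
- **That weeks 6 and 12 have no time zero.** The study-flow figure is not shown and the full protocol is not at hand. Either may settle this.

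**Conclusion.** The contradiction between the recruitment and randomization sections is real and rests on the text alone, with no assumption about timelines. Its importance depends on whether the exception is used. If it is, the trial is open to differential recruitment by staff who may know the arm, and the baseline NPI-12 constraint no longer applies to the analysed sample. If it is not, the randomization procedure stands. The size of any bias cannot be derived from the document, and sample size, alpha and power are untouched. The lag between baseline and allocation is a secondary matter of unknown length, which affects precision more than validity. The conflict should be resolved before homes are randomized, because differential recruitment cannot be undone in the analysis.

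**What to change.** - In the recruitment section, delete the closing three-word exception, so that screening, consent and baseline always precede disclosure.
- In the study design and randomization sections, state that enrolment and baseline close in all six homes before the allocation sequence is generated.
- State that any resident enrolled after disclosure is not part of the main between-arm comparison.
- Keep the enrolment block short, or repeat baselines that are old at allocation. The team should choose the permitted age, since the document gives no basis for a particular figure.

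The cost is a few sentences of protocol text. Enrolment may close slightly under 142, which is tolerable for a target described as a feasibility and planning figure, and some residents may need a second baseline.
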